### Adverse Event

For adverse events (AEs),∙adverse drug reactions (ADRs), serious adverse events (SAEs),∙serious adverse drug reactions (SADRs), unexpected adverse events∙, unexpected adverse events,∙collected during the study period, the number of subjects with events, the number of events, incidence rates, and two-sided 95% confidence intervals will be presented. The severity of the adverse events, the causal relationship with the investigational product, actions taken concerning the investigational product, other actions taken, and the outcomes of the adverse events will be summarized.

### Vital Signs

Descriptive statistics for vital signs will be presented at baseline, 12 weeks, and 24 weeks. Changes from baseline at 24 weeks will be analyzed using the Paired t-test or Wilcoxon signed rank test.

### Laboratory Tests

Descriptive statistics for laboratory tests will be presented at baseline, 12 weeks, and 24 weeks. Changes from baseline at 24 weeks will be analyzed using the Paired t-test or Wilcoxon signed rank test.

Additionally, the frequency and percentage of normal (Normal or NCS) and clinically significant abnormal (CS) changes will be summarized. Detailed information on subjects with clinically significant abnormal (CS) items will also be listed.

### Subgroup Analysis

If a subgroup analysis based on the characteristics of the subjects is required, each item can be analyzed similarly to the efficacy and safety evaluation variables (e.g., analysis of primary efficacy evaluation results by gender etc.).

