## Rationale

This study is a large-scale, prospective, multicenter, non-interventional database observational study aimed at observing the weight loss effects, efficacy, and safety of Envlo Tab./Envlomet SR Tab. in patients with Type 2 diabetes over 24 weeks.

As a single-arm observational study, the number of subjects was calculated using G*Power 3.1.9.7, referencing the mean and standard deviation of the changes in weight and body mass index (BMI) from baseline to 12 or 24 weeks from previous Phase 2 and Phase 3 clinical studies (Figure 2) ^20)^

[Assumptions]

- Effect size: 0.25 (Mean of difference 2.5, SD of difference 10.0)
- Power: 0.95
- α error: 0.05
- Drop-out rate: 30%

[figure not shown]

Figure 2. Sample Size Calculation (G*Power)

Based on previous studies, assuming an average weight change of 2.5 kg and a standard deviation of 10.0 for the intervention with Envlo Tab. or Envlomet SR Tab., the effect size is 0.25. Setting the power: 0.95, α error: 0.05, the total required sample size is estimated to be approximately 210 subjects. Considering a drop-out rate of about 15%, we plan to recruit around 240 subjects.

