### Safety Analysis Set

Subjects who meet the inclusion/exclusion criteria, have been enrolled in this study, received the investigational product at least once according to the approved indications, and have undergone safety evaluations will be included in the safety analysis set.

1. **Methods of Analysis**
2. **General Principles**

Continuous variables will be presented as descriptive statistics (number of subjects, mean, standard deviation, median, minimum, maximum), and categorical variables will be presented as frequencies and percentages. Unless otherwise specified, all tests will be two-sided with a significance level of 5%. All p-values will be reported to a maximum of four decimal places. If not exactly divisible, values will be rounded to two decimal places, rounding up at the third decimal place.

1. **Demographic and Baseline Characteristics**

For the demographic data (age, gender, etc.) and baseline characteristics of the study subjects, continuous variables will be presented as mean, standard deviation, median, minimum, and maximum values, while categorical variables will be presented as frequency and percentage.

1. **Efficacy Endpoints**

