### Primary Efficacy Endpoint

For body mass index (BMI) and weight, descriptive statistics will be presented at baseline and at 24 weeks. The change from baseline to 24 weeks will be analyzed using a Paired t-test or Wilcoxon signed rank test.

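### Subgroups are to be analysed by a separate before-after test in each level; such tests do not compare the levels, and with equal true weight loss exactly one sex would reach significance in about 40% of trials under the planning values and an assumed equal sex split

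*Protocol*

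**What the plan says.** The Subgroup Analysis paragraph in Protocol section 8.2 is one conditional sentence. It opens "If a subgroup analysis based on the characteristics of the subjects is required" and continues "each item can be analyzed similarly to the efficacy and safety evaluation variables (e.g., analysis of primary efficacy evaluation results by gender etc."

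The method it refers to is set out earlier in the same section. For the primary endpoint: "The change from baseline to 24 weeks will be analyzed using a Paired t-test or Wilcoxon signed rank test." The secondary and exploratory endpoints use the same pair of tests at weeks 12 and 24, and vital signs and laboratory values use them at week 24. Descriptive statistics accompany the tests. The General Principles add: "Unless otherwise specified, all tests will be two-sided with a significance level of 5" percent. The subgroup paragraph specifies nothing different.

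The planning values are in section 3.2, Rationale, which also describes the study as single-arm: "Effect size: 0.25 (Mean of difference 2.5, SD of difference 10.0"), power 0.95, and "the total required sample size is estimated to be approximately 210 subjects."

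**The concern.** Analysing the primary result by gender is normally meant to show whether the weight change differs between men and women. A test of change against zero among men and another among women answer two other questions: did men change, and did women change. With no control arm, nothing in either test contrasts the two groups.

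The p-value in each level reflects the size of that level as well as the size of the change. Two levels with identical mean change and SD can therefore fall on opposite sides of 5% because one is smaller. What is at stake is the reading of the subgroup tables: one significant sex and one non-significant sex looks like a differing effect when there may be none. The reverse also happens. When both levels are significant, a real difference between them can go unremarked.

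**Working it through.** **Inputs from the Protocol.** Mean change 2.5, SD of change 10.0, effect size 2.5 / 10.0 = 0.25, 210 evaluable (section 3.2); two-sided 5% (section 8.2, General Principles); paired t-test (section 8.2, Primary Efficacy Endpoint).

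**Assumed, because the Protocol does not give it.** The sex split, varied from 50:50 to 30:70. The true change is set equal in both sexes.

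**Step 1: reproduce the planned sample size.** The power of a two-sided paired t-test with n subjects is the probability that a noncentral t variable, with n − 1 degrees of freedom and noncentrality 0.25 × √n, exceeds the 5% critical value in absolute size. Power first reaches 0.95 at n = 210 (0.9501; at 209 it is 0.9492). This matches the Protocol.

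**Step 2: dependence on level size.** Suppose both sexes show exactly a mean change of 2.5 with SD 10.0. Then t = 0.25 × √n.
- n = 63: t = 1.98, critical value 2.00, p = 0.052.
- n = 147: t = 3.03, critical value 1.98, p = 0.003.

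The results are identical in kilograms, but one is significant and the other is not.

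**Step 3: how often exactly one sex is significant.** With p1 and p2 the power in each sex, P(exactly one) = p1(1 − p2) + p2(1 − p1).

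| Split of 210 | p1 | p2 | Exactly one | Both | Neither |
|---|---|---|---|---|---|
| 105 / 105 | 0.718 | 0.718 | 40.5% | 51.6% | 7.9% |
| 84 / 126 | 0.620 | 0.795 | 42.9% | 49.3% | 7.8% |
| 63 / 147 | 0.497 | 0.853 | 50.2% | 42.5% | 7.4% |

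For the equal split: 2 × 0.718 × 0.282 = 0.405. A simulation of 40,000 trials gave 40.3%.

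**Step 4: a direct comparison on the same data.** In that simulation a two-sample t-test of the changes, men against women, flagged a difference in 5.0% of trials, which is its nominal error rate.

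**Step 5: sensitivity.** The result depends strongly on the SD. At 105 per sex and change 2.5:

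| SD of change | Power per sex | Exactly one significant |
|---|---|---|
| 10 | 0.718 | 40% |
| 8 | 0.887 | 20% |
| 7 | 0.952 | 9% |
| 6 | 0.988 | 2% |
| 5 | 0.999 | 0.2% |

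The evaluable number matters less. With 240 enrolled and the 15% drop-out in the text of section 3.2, 240 × 0.85 = 204 remain, and the equal-split figure is 41.5%. With the 30% in the assumptions list of the same section, 240 × 0.70 = 168 remain, and it is 47%.

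**Step 6: the opposite failure at a small SD.** As an illustration on assumed values, take SD 5, 105 per sex, and true losses of 3.5 kg and 1.5 kg. Power per sex is above 0.999 and 0.861, so both tests are significant in about 86% of trials and show no sign of the 2 kg difference. A direct two-sample comparison has noncentrality 2 / (5 × √(2/105)) = 2.90 and power of about 82%.

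**The case against.** A reader might infer that the protocol will report men and women as differing in four trials in ten. The text does not support that. It is conditional and permissive, it sets no hypothesis about effect modification, and it contains no rule that calls subgroups different when one test is significant and another is not. The 40% is a rate of discordant significance. It becomes a false claim only if someone reads it as one. This objection stands.

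A reader might also fault the open choice of subgroups, the possibility of choosing them late, or the missing exploratory label. A statistical analysis plan commonly settles these, and it is not at hand, so they are not part of this point.

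Two further objections stand in part. The analysis carried over includes descriptive statistics, so level sizes, means and SDs would appear beside any p-value and a careful reader could compare them. That softens the problem, but these summaries still give no between-level estimate with its uncertainty. Also, the 40% rests on an assumed split and on the planning SD being the true one, and it drops sharply if the SD is smaller. That limits the figure but not the reasoning: at a small SD, both levels being significant is equally uninformative about whether they differ.

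The objection that this is only detail left for later does not stand. The paragraph names a method by reference, and that method does not make the comparison.

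**Conclusion.** The point holds as a narrow criticism of the stated method. Separate before-after tests in each level do not compare levels, and each p-value depends largely on level size. Under the protocol's own change, SD and evaluable number, with an assumed equal sex split and equal true loss, exactly one sex reaches significance in about 40% of trials, rising to 50% at 30:70. At an equal split it falls to 20% at SD 8 and 2% at SD 6. The method invites a mistaken reading of a difference; it does not itself declare one. Severity is minor: the primary result comes from the whole cohort and does not change.

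**What to change.** Replace the method in the Subgroup Analysis paragraph with wording such as: *For any subgroup analysis of a change from baseline, the mean change at week 24 and its 95% confidence interval are shown for each level. Levels are compared by a linear model of change on subgroup and baseline value, reporting the between-level difference with its 95% confidence interval. Within-level tests against zero are not used to claim a difference between subgroups.*

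The cost is a few lines of text and one model per subgroup, using data already collected (sex, weight and BMI, medication). The small downside is that a subgroup result can no longer be presented as significant on its own. The direct comparison also has limited power: with 105 per sex and SD 10.0, a true difference of 2.5 would be detected with power of about 0.44. The interval should therefore be read as an estimate, and a non-significant difference should not be taken as proof that the levels are alike.

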# Ethical Considerations and Administrative Procedures

## Investigator's Responsibilities

The investigator will conduct this observational study according to this protocol, the ethical principles outlined in the Declaration of Helsinki, and relevant domestic laws and regulations. The investigator is responsible for quality management of the study conducted at the research institution and for protecting the safety of study subjects. Written informed consent must be obtained from patients before they are enrolled in the study, and all related data must be documented.

## Ethics Committee/Institutional Review Board (IRB)

This clinical study must receive prior approval from the IRB for the protocol and all related matters before initiation. The IRB will review the ethical and medical validity of the study and provide written documentation of their decision to the investigator and the study sponsor. Any amendments or changes to the protocol during the study must be submitted to and approved by the IRB.

## Ethical Considerations

This clinical study will be conducted in accordance with the ethical principles based on the “Declaration of Helsinki (Ethical Principles for Medical Research Involving Human Subjects)” and in compliance with the Bioethics and Safety Act and related regulations, prioritizing the rights, safety, and welfare of the study subjects.

## Quality Assurance and Audit

The sponsor will implement quality assurance and quality control of clinical study data in accordance with the sponsor's standard operating procedures (SOPs) to ensure that the study is conducted, data are generated, recorded, and reported in compliance with the protocol, the Bioethics and Safety Act, and related regulations.

The auditor will conduct audits following the procedures below.

1. Audits will be conducted according to the safety regulations of pharmaceuticals [Appendix 4] and the Good Clinical Practice (GCP) standards to ensure the quality of the clinical study.
2. The auditor will verify that the eCRF is documented, modified, verified, and processed according to appropriate procedures and that the study is being conducted according to the study plan and objectives.
3. The auditor will confirm that the clinical study is conducted in compliance with the Bioethics and Safety Act, related regulations, and SOPs.
4. The auditor will prepare and review the audit report and submit it to the sponsor. Following the prescribed procedures, the audit report will be finalized, and an audit certificate will be issued.
5. If any violations are identified during the audit, the sponsor will take corrective actions and implement measures to prevent recurrence. If the investigator's continuous violations or serious violations are confirmed, the sponsor may suspend the clinical study participation of the relevant study sites.

## Subject Informed Consent

The subject information sheet and informed consent form may be used after approval of the IRB. The investigator must obtain consent for the use of information from the study subjects in accordance with the ethical principles based on the Declaration of Helsinki and the Bioethics and Safety Act standards. The investigator must fully explain the study to the subjects (or their representatives) and obtain written consent from the subjects before performing any study-related procedures. Consent must be obtained in a private setting (e.g., consultation room, examination room). The investigator should retain the original signed consent form in the investigator files, and provide a copy of the signed consent form and information sheet to the subject (or legally acceptable representative).

If the study subject has difficulties in communication due to lack of understanding or ability to express their intentions, written consent must be obtained from the subject’s legal representative. If a subject has no legally acceptable representative, a representative will be appointed in the order of spouse, immediate family, and non-immediate family; if there are more than one immediate or non-immediate family members, it should be decided under an agreement. If an agreement is not reached, the eldest shall be the representative.

Even if the legal representative provides consent, the study subject should also sign and date the consent form, if possible.

If the subject or representative is unable to read, a witness (impartial observer) should be present for the entire consent process. The subject or representative verbally consents to participate in the study, signs the consent form if possible, and the witness signs the form to confirm that the information was accurately conveyed to the subject or representative, that it was understood, and that the consent was given voluntarily.

If there are any changes to the subject information sheet and consent form during the study, re-approval from the IRB must be obtained.

## Approval and Amendment of the Protocol

Prior to initiation of the study, the investigator should obtain written approval from the IRB for related documents and procedures, including the protocol, subject information sheet, and informed consent, etc.

Any amendments to the approved study protocol must also be approved by the IRB at each stage of the clinical study. Subjects cannot be enrolled in the clinical study before the protocol is approved.

## Monitoring of Clinical Study Sites

The sponsor will conduct monitoring to protect the rights and welfare of the study subjects, ensure the accuracy, completeness, and verifiability of data reported by the principal investigator, and confirm compliance with the approved study protocol and relevant regulations.

Monitoring will be carried out by designated monitors through regular site visits and telephone contacts. During site visits, monitors will review source documents, investigational software management records, and the status of essential document files. They will also verify study procedures and records, and if any issues or violations are found, they will discuss appropriate corrections and actions with the principal investigator and sub-investigator.

Monitoring visits will be scheduled at appropriate times through consultation between the monitors, principal investigator, and sub-investigator. The principal investigator and sub-investigator will actively cooperate with the monitors, providing access to all source documents for verification against the eCRF.

## Confidentiality and Privacy Protection for Subjects

Study data will be stored in a locked research office. Subject’s medical record numbers and institution-specific enrollment numbers will be kept in separate files under the responsibility of the principal investigator and encrypted to prevent personal identification from the clinical study data. According to the Enforcement Rule of the Bioethics and Safety Act, records related to the clinical study will be stored for three years after the study is completed. After the retention period, documents containing personal information will be destroyed in accordance with Article 16 of the Enforcement Decree of the Personal Information Protection Act. Files containing personal information will be password-protected, and no identifying information about the subjects will be included in any publications of the study results.

## Measures to Protect the Safety of Subjects

Institutions should have the facilities and specialized personnel necessary to conduct this study and should be fully prepared to properly conduct the study.

The investigator should thoroughly check the health of each subject prior to enrollment into the study to ensure that subjects are eligible to participate in the study. Also, the investigator must thoroughly understand the study protocol and conduct the study accordingly. Every effort must be made to ensure the safety of study subjects, and in the event of any adverse events related to the study, the investigator must ensure that the subject receives the necessary tests and treatments immediately. In addition, the subjects should be monitored until the resolution of the AE or loss to follow-up, if necessary.

The treatment and care of the subjects' conditions should be conducted independently of this study and should continue based on clinical judgment during and after the study period.

This study does not present any risks beyond the routine treatment provided in a clinical setting. Therefore, there are no additional risks related to the study, and no extra compensation for the subjects is necessary. Both the Medical Service Act and the professional liability insurance of the principal investigator and relevant institutions provide sufficient protection for both study subjects and participating researchers.

Since this study does not provide investigational drugs to the subjects, any drug-related compensation will follow the existing legal responsibilities for the drugs.

## Utilization and Publication of Study Results

In principal, all data and results generated during the study period are owned by the sponsor, who is to report and publish them. The sponsor will prepare a final report of the study results according to the protocol and notify the investigators.

Investigators must not publish, present, or disclose any results related to this study without prior written consent from the sponsor.

If the investigator intends to present or publish the study results in academic journals, they must obtain approval from the sponsor, who retains the right to review the content before deciding to make it public.

## Roles and Responsibilities of the Principal Investigator

The principal investigator is responsible for the overall quality management of the study and the protection of the study subjects' safety. He/She will review key study documents, oversee matters arising at each participating site, and coordinate opinions among participating institutions and investigators. The principal investigator is also responsible for obtaining IRB approval before the study commences and for reporting to the IRB during the study, upon completion, and regarding the study results.

